### Criteria for discontinuing or modifying allocated interventions

Participants will not be considered as having withdrawn from the study in the following cases, and they will be eligible for protocol evaluation unless they withdraw their consent for assessments:If the participant requests to discontinue the program treatment;If the participant is unable to continue the program treatment due to adverse events;When the researcher considers that the risks of continuing the program treatment outweigh the benefits for any reason; andFor any of the other reasons, the researcher deems it unsuitable to continue the program treatment.

### Adherence

The intervention group participants will use WeChat mini-program to log in and complete the intervention sessions according to the plan. The completion of each course will be tracked through the mini-program. The “diary check-in” function in the mini-program will provide positive and constructive feedback to participants to improve compliance. Investigators will be able to “check-in” from the dashboard, and regularly track their learning, medication, and lifestyle blood sugar control behaviors.

### Ancillary for post-trial care

As for the nature of digital patient education, participants are unlikely to be harmed. Once a risk of harm is identified, the principal investigator will intervene to reduce the risk of harm. If any harm is discovered, the research team will appropriately compensate participants as necessary.

### Outcomes

#### Primary outcome measures

The primary endpoint is to compare the difference in HbA1c levels among the three groups at the 3-month follow-up. After enrollment, the HbA1c levels will be recorded at baseline and at the end of the first, second, and third digital intervention cycles.

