**Methods:**

This trial is a prospective randomized controlled trial conducted at the First People’s Hospital of Kunshan City from April 1, 2023, to December 31, 2024, with a follow-up period of 3 months. The specific randomization method was established and implemented through the EDC clinical trial center’s randomization system. We will measure and collect baseline data from three groups, including Group A: digital intervention + virtual incentives + conventional treatment, Group B: digital intervention + physical incentives + conventional treatment, and Group C: conventional treatment. HbA1c, weight, SMBG testing rate, diabetes self-efficacy, and diabetes-related medical expenses will be recorded at baseline, 1 month, 2 months, and 3 months for all three groups. The Shapiro-Wilk test will be used to test for normality, and Pearson correlation analysis will be used for correlation analysis. Dropouts will be analyzed separately. Analysis of variance or exact probability calculation will be used to compare demographic data and other baseline indicators.

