### Participant timeline

The schedule of the participants is shown in the Table 1.

**Table 1 Tab1:** The schedule of the participants

Period	Baseline screening	Follow-up period			
Interview	1	2	3	4	5
Days	-7~-1	1	28 ± 5	56 ± 5	84 ± 5
Informed consent	√				
Baseline characteristics	√				
Physical exams/urinalysis/ Kidney and liver functions	√				
H1Abc	√				√
Inclusion exclusion criteria review	√				
Random allocation		√			
Digital intervention^1^		√	√	√	√
Conventional therapy		√	√	√	√
Incentives^2^			√	√	√
SMBG testing rate^3^			√	√	√
Weight^4^			√	√	√
Scale evaluation^5^		√	√	√	√
Medical expenses^6^		√	√	√	√
Adverse events evaluation		√	√	√	√

(1) Digital intervention: implementation of the WeChat mini-applet. (2) Incentives: patients will be given incentive content at the end of each monthly follow-up. (3) Calculation of testing rate: self-blood glucose monitoring once every morning on an empty stomach, continuous monitoring for 3 months, detection rate = actual measurement times/expected measurement times, and data recorded in the SMBG diary card. (4) Weight: measured at the clinic during each follow-up visit. (5) Scale evaluation: completed the scale evaluation under the doctor’s instructions. (6) Diagnosis and treatment expenses: during the 3-month period, all medical expenses related to diabetes diagnosis and treatment, including outpatient and inpatient visits, will be recorded

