### Assignment of interventions

Participants and investigators will be informed about the interventions assigned to them in this open-label trial. Due to the nature of the patient-reported outcome indicators, not all outcome evaluations will be blinded. Assignment will not be known to statisticians during the analysis. As this is an open-label trial, no blind-breaking procedures will apply.

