### Data collection

Data will be collected at the study site using EDC. Data will be collected at a total of 5 time points: baseline, intervention period day 1, day 28±5, day 56±5 and day 84±5. The data collected will be stored in the form of an electronic CRF. Investigators will be informed of any changes made by the CRC and the system will automatically perform a system/edit check. Authorized investigators will be given access to the study computer and will evaluate the data throughout the course of the study. If any missing data is detected through the EDC system, the investigator will contact the participant by telephone.

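### Table 1 contradicts the text on when HbA1c and weight are collected: no HbA1c at months 1 and 2, and no scheduled pre-intervention weight

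*Protocol article*

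**What the plan says.** Two places in the text set the collection times. For the primary outcome, "the HbA1c levels will be recorded at baseline and at the end of the first, second, and third digital intervention cycles". The Interventions section defines three monthly cycles, so the first two end at Interviews 3 and 4. The Methods paragraph of the abstract extends this to every outcome: "HbA1c, weight, SMBG testing rate, diabetes self-efficacy, and diabetes-related medical expenses will be recorded at baseline, 1 month, 2 months, and 3 months".

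Table 1 (Participant timeline) has five interviews: screening, day 1, and days 28, 56 and 84. HbA1c is ticked at the first and last only. Weight is ticked at the last three, and note 4 describes it as "measured at the clinic during each follow-up visit". The scale evaluation is first ticked on day 1, the visit that also carries "Random allocation". The Data collection section treats screening and day 1 as distinct: "Data will be collected at a total of 5 time points: baseline, intervention period day 1, day 28±5, day 56±5 and day 84±5". On masking: "Participants and investigators will be informed about the interventions assigned to them in this open-label trial".

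Three other statements matter. Under Secondary outcome measures, weight and self-efficacy are between-group comparisons at 3 months. Statistical methods also plans a within-group comparison from before to after the intervention. The same section leaves missing values as they are and analyses observed cases only.

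**The concern.** Staff working from Table 1 and staff working from the text would collect different data on the primary variable. A reader of the results could not tell whether absent month-1 and month-2 HbA1c values were missed or never due.

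For weight, the first scheduled value comes after four weeks of intervention. A before-after change then has no scheduled starting value. The month-3 comparison also loses the most useful covariate that a weight outcome can have. If an analyst filled the gap with day-28 weight, adjustment would remove whatever part of the effect had appeared in the first month. No section proposes this, but the schedule offers no other early value.

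**Working it through.** **Step 1. Promised against scheduled times.** Each Table 1 row was split by column and set against the abstract and the outcomes section.

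| Item | Promised in text | Ticked in Table 1 | Gap |
|---|---|---|---|
| HbA1c | baseline, months 1, 2, 3 (4 times) | screening, day 84 (2 times) | months 1 and 2 |
| Weight | baseline, months 1, 2, 3 (4) | days 28, 56, 84 (3) | baseline |
| Self-efficacy | baseline, months 1, 2, 3 (4) | days 1, 28, 56, 84 (4) | first value shares the allocation visit |
| SMBG rate | baseline, months 1, 2, 3 (4) | days 28, 56, 84 (3) | baseline |
| Expenses | baseline, months 1, 2, 3 (4) | days 1, 28, 56, 84 (4) | first value on day 1; no consequence claimed |

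The pattern is not an artefact of text extraction. The HbA1c row keeps blank cells between its two ticks, and the neighbouring rows keep their column positions.

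**Step 2. What the HbA1c gap costs.** The primary endpoint is the 3-month comparison, and day 84 is ticked. Under the observed-case rule, a patient lost after month 1 or 2 is absent from that comparison whether or not interim HbA1c was measured. Interim values would help only in a repeated-measures model that uses those visits, and the article does not plan one.

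**Step 3. What the weight gap could cost.** The article gives no figure to reproduce: the Sample size section states no SD or effect size, and it concerns HbA1c. The following is illustrative.

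- Evaluable per arm: 100 × (1 − 0.20) = 80, from the Sample size section.
- Two-sided α = 0.05, power 80%, one pairwise comparison.
- Detectable standardised difference: (1.960 + 0.842) × √(2/80) = 2.802 × 0.1581 = 0.443. With the t distribution it is about 0.446. Both are about 0.45 SD.
- Adjusted for baseline weight with correlation r: multiply by √(1 − r²).
- r = 0.95 (assumption): √(1 − 0.9025) = 0.312, so 0.446 × 0.312 = 0.14 SD.
- r = 0.97 (assumption): √(1 − 0.9409) = 0.243, so 0.446 × 0.243 = 0.11 SD.
- In kilograms, for an assumed SD of 10 to 15 kg: 4.5 to 6.7 kg unadjusted, against 1.1 kg (SD 10, r = 0.97) to 2.1 kg (SD 15, r = 0.95) adjusted.

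A lower r gives a smaller gain. The gain comes from having a baseline weight and also putting it in the model; a tick in the table alone changes nothing.

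**Step 4. Self-efficacy and SMBG.** Scale and allocation fall on the same visit of an open-label trial, and their order is not stated. Taking the scale row to be the self-efficacy scale is an inference, since no other scale outcome is named. For SMBG, note 3 defines the rate over the three months of trial monitoring, so a baseline rate has no definition.

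**The case against.** The strongest reply is that little of consequence follows. The outcomes are 3-month between-group comparisons, and a randomised comparison of month-3 weight is valid without a baseline. Weight may well have been taken at Interview 1, where physical examination and baseline characteristics are ticked, and a condensed article need not list every item of an examination. The order of procedures within a visit is commonly left to the full protocol. Recruitment was expected to end by December 15, 2023, before publication on February 1, 2024, so new baseline readings may no longer be possible.

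Most of this stands, and it rules out several stronger readings:

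- **That the primary endpoint is not collected, or that the missing HbA1c ticks cause dropouts to be lost.** Both required HbA1c times are scheduled, and it is the observed-case rule that removes lost patients. The 20% dropout allowance therefore does not measure the effect of this gap.
- **That no baseline weight exists.** The article shows only that none is scheduled by name.
- **That self-efficacy was answered after the arm was known.** The order is unstated, which leaves a pre-allocation answer possible but not secured.
- **That the trial loses a definite number of kilograms of sensitivity for weight.** SD and correlation are assumed, and the article does not plan baseline adjustment.

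The reply does not remove the contradiction itself. The article states both HbA1c schedules, so this is not detail left to another document. Note 4 does not rescue baseline weight either: Table 1 places day 1 under the follow-up heading, yet weight is not ticked there.

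**Conclusion.** The point holds as a text-table contradiction. HbA1c is promised four times and scheduled twice. Weight is promised at baseline and first scheduled at day 28, so the planned before-after change has no scheduled pre-intervention value. This follows from the article alone and needs no assumption.

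The month-3 primary comparison remains scheduled. The cost for weight is one of precision, and its size is illustrative: about 0.45 SD detectable without adjustment, and 0.11 to 0.14 SD if r lies between 0.97 and 0.95, for 80 per arm and a single pairwise test. The timing of the self-efficacy scale and the baseline SMBG rate are minor points of clarification. The whole should be corrected, but it does not put the primary result in doubt.

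**What to change.** 1. **HbA1c.** Reconcile the abstract and the Primary outcome measures section with Table 1. Either tick Interviews 3 and 4, or remove months 1 and 2 from the text. If interim values are kept and are meant to help with dropout, replace the observed-case rule for HbA1c with a repeated-measures model that uses those visits.
2. **Weight.** Schedule a reading before allocation, at Interview 1 or at Interview 2 before randomisation. For patients already enrolled, retrieve it from the screening examination where it was recorded. Name it as covariate in the month-3 weight comparison, and state that day-28 weight will not serve as baseline. Report how many patients have a retrieved value, and give the unadjusted comparison alongside, since the observed-case rule would drop the others from the adjusted model.
3. **Self-efficacy (minor).** State that the day-1 scale is completed before allocation. Where the order is unknown, do not treat that score as a pre-allocation baseline.
4. **SMBG rate (minor).** Remove its baseline from the abstract.

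The cost is a table and text correction, a record search for enrolled patients, and one weight reading at an existing visit for anyone not yet randomised. Keeping monthly HbA1c adds only the laboratory cost that the text already implies.

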#### Secondary outcome measures

At the 3-month follow-up, the difference in SMBG testing rate among the three groups will be compared;At the 3-month follow-up, the difference in weight among the three groups will be compared;At the 3-month follow-up, the difference in diabetes self-efficacy among the three groups will be compared;At the 3-month follow-up, the difference in diabetes-related diagnosis and treatment expenses among the three groups will be compared.

### Participant timeline

The schedule of the participants is shown in the Table 1.

**Table 1 Tab1:** The schedule of the participants

Period	Baseline screening	Follow-up period			
Interview	1	2	3	4	5
Days	-7~-1	1	28 ± 5	56 ± 5	84 ± 5
Informed consent	√				
Baseline characteristics	√				
Physical exams/urinalysis/ Kidney and liver functions	√				
H1Abc	√				√
Inclusion exclusion criteria review	√				
Random allocation		√			
Digital intervention^1^		√	√	√	√
Conventional therapy		√	√	√	√
Incentives^2^			√	√	√
SMBG testing rate^3^			√	√	√
Weight^4^			√	√	√
Scale evaluation^5^		√	√	√	√
Medical expenses^6^		√	√	√	√
Adverse events evaluation		√	√	√	√

(1) Digital intervention: implementation of the WeChat mini-applet. (2) Incentives: patients will be given incentive content at the end of each monthly follow-up. (3) Calculation of testing rate: self-blood glucose monitoring once every morning on an empty stomach, continuous monitoring for 3 months, detection rate = actual measurement times/expected measurement times, and data recorded in the SMBG diary card. (4) Weight: measured at the clinic during each follow-up visit. (5) Scale evaluation: completed the scale evaluation under the doctor’s instructions. (6) Diagnosis and treatment expenses: during the 3-month period, all medical expenses related to diabetes diagnosis and treatment, including outpatient and inpatient visits, will be recorded

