### Interventions

To compare the effects of digital intervention based on behavioral economics theory on HbA1c, SMBG testing rate, and diabetes self-efficacy in patients with T2DM, conventional treatment was used as a control intervention. Conventional treatment was administered according to the T2DM conventional drug treatment method recommended by clinical guidelines. Conventional drugs include but not limited to metformin, sulfonylureas, glinides, α-glycosidase inhibitors, TZDS, DPP-4i, SGLT2i, GLP-1RA, and insulin. Digital intervention refers to the use of WeChat mini-program in smartphones to provide patients with out-of-hospital coordinated management based on cognitive behavioral therapy, guiding patients to improve their health behaviors in coping with diabetes and enhance the level of blood glucose self-management. The main content includes disease knowledge courses, auxiliary training courses (diabetic diet essentials), psychological counseling courses, course Q&A games, and relevant behavior records (daily attendance, medication check-ins, daily sugar control diet punch card). From day 1 to 1 month of the study is the first cycle, to 2 months is the second cycle and to 3 months is the third cycle.

After completing a single cycle of digital intervention, the subjects who receive digital intervention can receive virtual and tangible incentives respectively. On the first day of each cycle, the incentive content to be received at the end of the cycle will be reminded during follow-up. The subjects need to provide self-recorded and completed SMBG diaries to the researchers to receive incentives after check-in. The virtual incentive is a healthy behavior learning badge that lights up each cycle, including bronze, silver, and gold, which are awarded in turn according to the user’s completion (≥70%, ≥80%, ≥90%) judged by the researcher. The tangible incentive is a health behavior auxiliary tool provided each cycle, including an electronic medication box, a weight scale, and a smart bracelet, which are awarded in turn according to the user’s completion (≥70%, ≥80%, ≥90%) judged by the researcher.

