### Sequence generation

In this randomized controlled trial, a simple randomization method was used to allocate participants to three groups with a 1:1:1 allocation ratio. Group A: digital intervention + virtual incentives + conventional treatment, Group B: digital intervention + physical incentives + conventional treatment, and Group C: conventional treatment. A central randomization system for the EDC clinical trial is established and implemented. Randomizers at the trial center will access the system with an account number and password, enter basic information about the subject patients and generate a randomization number for follow-up.

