Missing values will not be replaced or added. All analyses will be based solely on observed cases. Patients lost to follow-up will be considered to have dropped out of treatment. Only PP patients will be used in sensitivity analyses to test the impact of this assumption. No genetic or molecular analysis will be performed in this trial or future use.

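### The cycle-3 reward is given at the visit that measures the primary HbA1c, so attendance there may be rewarded unequally by arm and by completion, mainly in Group B

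*Protocol article*

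**What the plan says.** **Timing.** In the Participant timeline section, Table 1 ticks the incentive row at Interviews 3, 4 and 5 (days 28, 56 and 84). Footnote 2 states that "patients will be given incentive content at the end of each monthly follow-up". Footnote 4 has weight taken in the clinic at each follow-up, so these are clinic visits. The HbA1c row is ticked only at screening and at Interview 5. The primary outcome section reads: "The primary endpoint is to compare the difference in HbA1c levels among the three groups at the 3-month follow-up".

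**Who is eligible.** The Interventions section says that "the subjects who receive digital intervention can receive virtual and tangible incentives respectively", which means Groups A and B. Sequence generation closes its list of arms with "and Group C: conventional treatment" and attaches no incentive to it. The rewards are "awarded in turn according to the user’s completion (≥70%, ≥80%, ≥90%) judged by the researcher". There is a further condition: "The subjects need to provide self-recorded and completed SMBG diaries to the researchers to receive incentives after check-in".

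**What the reward is.** For Group A, "The virtual incentive is a healthy behavior learning badge that lights up each cycle". For Group B it is one physical item per cycle.

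**Analysis.** Statistical methods states: "All analyses will be based solely on observed cases". Missing values are not filled in. The only sensitivity analysis uses the per-protocol set, defined as patients who completed the three-month examination.

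**The concern.** Rewarding behaviour is the intervention under test, and it is meant to differ between arms. An effect of rewards on behaviour is part of the treatment effect. An effect of rewards on whose HbA1c gets measured is selection.

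Giving the last reward at Interview 5 mixes the two. A Group B patient who met the threshold has an item waiting at that visit. A Group B patient who fell short has none, and neither does anyone in Group C. If this changes who attends, and if completion is related to HbA1c, the observed Group B mean no longer represents the randomised Group B. Both B versus C and B versus A could be affected. The Introduction names the comparison of monetary with non-monetary rewards as an aim.

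The stated analysis would not reveal this. Observed cases are the attenders, and the per-protocol set consists of attenders again.

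**Working it through.** **1. The plan's own figures.** The Sample size section gives 100 per group and 20% dropout, so 100 × (1 − 0.20) = 80 evaluable per group. The article states no HbA1c difference or SD, so the 100 cannot be rebuilt. The point does not depend on it.

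**2. Model.** Everything in this step is assumed. Let q be the share of an arm that meets the reward threshold, a1 and a0 the day-84 attendance above and below it, and D the HbA1c gap between the two subgroups. Then:

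- overall attendance a = q·a1 + (1 − q)·a0
- share above the threshold among those observed = q·a1 / a
- shift of the observed arm mean = D × (q·a1/a − q) = D × q(1 − q)(a1 − a0) / a

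The control arm is taken to have 80% attendance unrelated to HbA1c.

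As a plausibility check on D, the Evidence before this study section cites a trial with 0.016 points lower HbA1c per extra day of app use. Assumed gaps of 20 to 50 days give 0.016 × 20 = 0.32 to 0.016 × 50 = 0.80. That is an association only.

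**3. Results at the planned 20% loss** (a = 0.80, q = 0.5; shift in HbA1c points, towards apparent benefit)

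| a1 / a0 | q·a1/a − q | D = 0.3 | D = 0.6 | D = 0.8 | D = 1.0 |
|---|---|---|---|---|---|
| 0.80 / 0.80 | 0 | 0 | 0 | 0 | 0 |
| 0.85 / 0.75 | 0.031 | 0.009 | 0.019 | 0.025 | 0.031 |
| 0.90 / 0.70 | 0.0625 | 0.019 | 0.038 | 0.050 | 0.063 |
| 0.95 / 0.65 | 0.094 | 0.028 | 0.056 | 0.075 | 0.094 |

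Example: 0.5 × 0.95 / 0.80 = 0.594; 0.594 − 0.5 = 0.094; with D = 0.6 the shift is 0.056.

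Since q(1 − q) is largest at q = 0.5, a stricter threshold (smaller q) does not raise these values for the same D and attendance gap. With q = 0.7, a 30-point gap and D = 0.8, the shift is 0.8 × 0.21 × 0.30 / 0.80 = 0.063.

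**4. False-positive rate.** Take 80 per arm, no true effect and an assumed SD of 1.0, so SE = √(2/80) = 0.158. A shift of 0.075 is 0.075/0.158 = 0.474 SE. The two-sided rate per comparison becomes Φ(−1.96 + 0.474) + Φ(−1.96 − 0.474) ≈ 0.076, against 0.050. With SD 1.2 it is 0.068. At the corner of the table (0.094, SD 1.0) the ratio is 0.593 and the rate is about 0.086 + 0.005 = 0.091.

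**5. Larger losses.** With a1 = 0.95 and a0 = 0.50, the shift is 0.093 (D = 0.6) to 0.155 (D = 1.0). Overall attendance is then 0.5 × 0.95 + 0.5 × 0.50 = 0.725, a loss of 27.5%, which exceeds the planned 20%.

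**6. Can analysis repair it?** In this model attendance depends only on completion. Weighting the two observed subgroup means by q and 1 − q returns the true arm mean, so the shift disappears. The Adherence section says course completion is tracked in the mini-program, so the information should exist for A and B. The stated analysis does not use it.

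**The case against.** **Collection in person is inferred.** Footnote 2 says when the incentive is given; no sentence makes attendance a condition. The check-in mentioned with the diary hand-over may be a mini-program function, as the term is used under Adherence. This stands, and is why the point says attendance may be rewarded. Handing over goods and diaries at a clinic visit is still the natural reading for Group B.

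**Group A hardly fits.** A badge that lights up needs no visit. This stands. A reader might infer that both digital arms are flattered alike; the documents do not support that.

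**The threshold is unclear.** The award wording could mean 70% in every cycle, or a threshold rising to 90% by cycle 3. A flat 70% rule at day 84 cannot be stated as fact.

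**Other reasons to attend exist.** Conventional therapy, weight, scales and adverse-event review are ticked at Interview 5 without restriction by arm. Patients who stop the programme remain eligible for evaluation, and missing data prompt a telephone call. Visit reimbursement may be in the full protocol. All this weakens the pull, but a call cannot supply an HbA1c value.

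**The arithmetic credits the whole attendance gap to the reward.** Adherent patients may attend more often anyway, and selective attendance in Group C could offset or reverse the net shift. This stands, so the table bounds a scenario and does not estimate a bias.

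**Conclusion.** The structural point holds. The last reward coincides with the primary-endpoint visit, it is open only to A and B patients who meet completion and diary conditions, and the stated analyses can neither detect nor correct reward-driven attendance.

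Its size and direction are not given by the documents. With q = 0.5, D up to 1.0 point, an attendance gap of 0 to 30 points, 20% overall loss and unselected attendance in Group C, the shift is about 0 to 0.09 HbA1c points. The concern is mainly for Group B.

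Two stronger readings are tempting. One is a distortion of up to about 0.16 points; that needs 27.5% loss in the digital arms. The other is that analysis could only partly repair it; in the model used here, weighting by tracked completion removes it fully.

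The Primary outcome measures section also has HbA1c recorded after every cycle, whereas Table 1 ticks it only at screening and day 84. These passages need reconciling, but on either reading day 84 is both the endpoint visit and a reward visit. This is a cheap improvement, not a fatal flaw.

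**What to change.** **Conduct.**
- Make the cycle-3 reward depend on completion data and not on attending Interview 5. For example, deliver Group B's item separately; Group A's badge can simply light up in the mini-program.
- State which completion threshold applies at cycle 3.
- Give all three arms the same small attendance compensation for Interview 5, whatever their completion.

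**Analysis, for patients already past day 84.** The Trial status section expected recruitment to end by 15 December 2023, so on schedule the last day-84 visits would fall in early March 2024 and this part may matter most.
- Report day-84 HbA1c availability by arm and, in A and B, by completion.
- Add a missing-data sensitivity analysis on all randomised patients that uses baseline HbA1c and tracked completion, in place of relying on the per-protocol set alone. Group C has no mini-program completion, so there it must rest on baseline HbA1c and other recorded data.

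**Cost.** A modest budget line: delivery of one item per eligible Group B patient and an identical small payment for up to 300 patients, plus protocol wording. The control arm would receive a small completion-independent payment, and adherent Group B patients may feel less pull to attend. The analysis part needs no new data.

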## Discussion

This paper describes in detail a parallel randomized controlled trial designed to assess the impact of digital intervention based on behavioral economics theory on indicators such as HbA1c, SMBG detection rates, and diabetes self-efficacy in patients with T2DM. Digital health care has been widely used in health systems, particularly during the COVID-19 pandemic, and to reduce the risk of virus transmission between patients and clinicians, many health systems have rapidly converted more than 70% of outpatient cases to digital care via telephone or video transmission [20, 21]. However, concerns remain that chronic disease management delivered through digital processes may be of poor quality, difficult for patients to use proactively and spontaneously, and may exacerbate health disparities. To improve digital chronic disease management even more, we think that digital intervention based on behavioral economics theory is a feasible way to improve HbA1c levels in patients with T2DM. Such digital interventions integrate multidisciplinary theories. We hypothesized that digital intervention based on behavioral economics theory would be effective in improving SMBG detection rates and diabetes self-efficacy in T2DM patients. The significance of this study is that, until now, research on digital intervention and patients with T2DM has been limited to the hospital setting. No studies have yet reported the effectiveness of digital intervention based on behavioral economics theory in T2DM patients outside the hospital. As behavioral economics theory highlights that people are influenced by cognitive biases and emotional factors when making decisions, the intervention process will be gamified and is expected to increase patients’ interest in using it. In addition, this study may demonstrate that a digital intervention based on behavioral economics theory can reduce the financial burden on T2DM patients. Moreover, there are some limitations to this study. This study excluded T2DM patients treated with multi-drug combinations and only included T2DM patients who were stably treated with mono-therapy. Future studies may involve a larger group of patients. Secondly, due to the nature of the study, it was not possible to use blinding among participants and staff (excluding statisticians) during digital administration, which may have biased the expected effect of treatment.

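### The self-efficacy scale is completed under the instructions of a doctor who knows the arm, an avoidable influence of unknown size on a subjective secondary outcome

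*Protocol article*

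**What the plan says.** All references are to the protocol article.

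- **How the scale is given.** Participant timeline, Table 1, note 5 opens "Scale evaluation: completed the scale evaluation under the doctor" and ends by making the instructions the doctor's. The table marks the scale at day 1 and at the day 28, 56 and 84 visits, without distinguishing arms.
- **Which outcome this is.** The table does not name the scale. Among the primary and secondary outcomes, diabetes self-efficacy is the only one that needs a questionnaire. It is one of four secondary outcomes, compared between the groups at 3 months.
- **Who knows the arm.** Assignment of interventions: "Participants and investigators will be informed about the interventions assigned to them in this open-label trial". The Discussion adds that neither participants nor staff could be blinded, with statisticians the only exception.
- **The reason given.** Assignment of interventions: "Due to the nature of the patient-reported outcome indicators, not all outcome evaluations will be blinded".
- **What else happens at these visits.** Under Interventions, patients in the digital arms hand in glucose diaries to obtain a badge (A) or an item (B), at a level of completion "judged by the researcher". Table 1 marks incentives at days 28, 56 and 84, and its note 2 places them at the close of each monthly visit. Group C has no incentive.
- **What the team expects.** In the Discussion, the hypothesis is that the digital intervention "would be effective in improving SMBG detection rates and diabetes self-efficacy in T2DM patients".

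**The concern.** Self-efficacy is a self-rating and can move with what the patient thinks the listener wants to hear. In an open-label trial the patient's knowledge of the arm already puts such an outcome at risk, and nothing can remove that. Note 5 adds a second route, a doctor who also knows the arm and who directs completion of the form.

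An influence that is the same in every arm would cancel in the comparison. The worry is that it may not be the same. Patients in A and B have their programme completion assessed and rewarded around the same visits, by a study team that has stated an expectation of improvement. Patients in C are not in that position. Any prompting or social-desirability effect could therefore differ by arm, and the likelier direction is in favour of A and B. At stake is how the 3-month self-efficacy comparison can be read. The HbA1c comparison is not at stake.

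**Working it through.** The plan gives no figure on this point to reproduce. The check is a reading of the sections together, followed by an illustration of scale.

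**Reading the sections together**

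1. Note 5 fixes a mode of administration, so this is a stated choice and not a detail left to a fuller document.
2. Self-efficacy is the only listed outcome that needs a scale, so note 5 governs it. This is an inference, but no other listed outcome fits.
3. Investigators are told the assignment, and only statisticians are masked. The doctor in note 5 therefore knows the arm.
4. The reason given for incomplete blinding is the patient-reported nature of the outcomes. That accounts for the patient. It does not account for the doctor, because a self-report form can be completed without one.
5. The scale and the incentives share the day 28, 56 and 84 visits. Note 2 puts the incentive at the close of the visit. Where the diary hand-in and completion review fall relative to the scale is not stated.
6. The first scale reading is on day 1, the day of random allocation. The order within that day is not stated either.

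**Illustration of scale only**

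Inputs from the Sample size section: 100 per group, 20% dropout, alpha 0.05 (taken as two-sided), power 80%. That sample size was set for HbA1c. The documents give no scale, standard deviation or effect for self-efficacy, so the shifts below are **assumed**, in standard deviation (SD) units.

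- Evaluable per group: 100 × (1 − 0.20) = 80.
- Standard error of a pairwise difference: √(2/80) = 0.158 SD.
- Pairwise difference detectable at 80% power: (1.960 + 0.842) × 0.158 = 0.443 SD.
- With no true effect and an arm-related reporting shift *s*, the chance of a significant pairwise result is 1 − Φ(1.960 − *s*/0.158) + Φ(−1.960 − *s*/0.158).
- For *s* = 0.1, *s*/0.158 = 0.632, which gives 1 − Φ(1.328) + Φ(−2.592) = 0.097.

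| Assumed total shift (SD) | Pairwise test, one arm shifted | Three-group ANOVA, A and B both shifted against C |
|---|---|---|
| 0 | 5.0% | 5.0% |
| 0.1 | 9.7% | 9.2% |
| 0.2 | 24.4% | 23.6% |
| 0.3 | 47.5% | 48.1% |

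The ANOVA column uses the noncentral F distribution with 80 per group. The table shows that a trial of this size is sensitive to modest reporting shifts. It covers the *total* arm-related shift, most of which may come from the patient's own knowledge of the arm. It says nothing about how large the doctor's part is.

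**The case against.** The strongest reply is that note 5 is one short footnote which fits a doctor who explains the form and then leaves the patient to it. The article says nothing about reading items aloud, seeing answers or staying in the room. Scripts, privacy and visit order are commonly left to site instructions, and their absence is no finding. Group C completes the same scale in the same way, so a common influence cancels. The Discussion already admits that lack of blinding may bias results. With primary-school education as the entry threshold, there is also a plausible reason for having someone explain the scale.

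Much of this stands, and it rules out several stronger readings that a reader might infer:

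- *That the doctor supervises or sees the answers.* The text speaks only of instructions.
- *That the doctor is the person who decides the reward.* Note 5 says doctor and the Interventions section says researcher. No section says they are the same person.
- *That the reward comes before the scale.* Note 2 can be read the other way.
- *That a main hypothesis or every follow-up reading is compromised.* HbA1c is primary. Self-efficacy is one of four secondary outcomes, and its endpoint is the 3-month comparison.
- *That the bias is 0.1 to 0.3 SD, or a given share of the detectable 0.443 SD.* The range is assumed, and the denominator comes from a sample size planned for HbA1c.

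What the reply does not answer is that an arm-aware doctor's involvement is written into the plan, the reason given for incomplete blinding does not call for it, and the general limitation in the Discussion does not address it. Equal procedure in all arms does not guarantee equal influence when the person giving the instructions knows the arm.

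**Conclusion.** The point holds as a modest, avoidable weakness in how one subjective secondary outcome is collected. The documents support three statements: a doctor instructs completion, that doctor knows the arm, and the justification offered covers only the patient. That the effect could differ by arm is a reasonable inference from the completion review and incentives in A and B, but it is not shown. Its size is unknown and cannot be separated from the effect of the patient's own knowledge of the arm, which would remain after any change. The conclusion rests on two assumptions: that the unnamed scale in Table 1 is the self-efficacy scale, and that instructions means some contact about the form at the visit. The documents do not support a conclusion that the self-efficacy result is invalid, and the primary analysis is untouched.

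**What to change.** Replace note 5 with wording such as: *Self-efficacy scale: completed by the patient alone on arrival, from fixed written instructions identical in all groups, before contact with the doctor and before any review of diary, programme completion or reward. Staff check only for blank items and answer questions of comprehension from a neutral script.*

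The cost is a change in visit order and one line of instruction, with no extra staff. Entry already requires literacy and smartphone use, so self-completion is feasible. The downside is slightly more blank or misunderstood items among patients with primary-school education. This matters because the Statistical methods rule out imputation and analyse observed cases only. The check for blanks and the scripted answers limit that loss, though they leave some contact with unmasked staff.

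Recruitment was expected to end on 15 December 2023, so the last day 84 + 5 visits would fall in about mid-March 2024, and many readings may already have been taken. For those, the sponsor should state what the doctor's instructions consisted of and whether they were the same in all arms, and should report the mode of administration alongside the self-efficacy result.
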